#### 2.6.4 Missing data

Most of the variables required for the proposed analysis, with the exception of some demographic variables such as age, sex and place of residence, are based on the presence of ICD-10 codes or similar codes in the BARMER data. As such they are not subject to have known missing data. For example, if an individual does not have any ICD-10 codes related to an influenza infection, the individual will be coded as not having experienced a medically attended influenza. Although it is possible that the individual *did* experience a medically attended influenza that was not properly recorded in the claims data, these “missing” data entries will not be known to us. Nevertheless, because all such variables we are interested in are relevant for proper accounting, we believe that this is a very minor issue. Preliminary analysis through the course of the VAC-MAC project additionally indicate that the amount of missing data in demographic variables is negligible. Accordingly, individuals with missing data will simply be removed from the analysis without the use of imputation based or similar strategies (70).

#### 2.6.5 Assumptions

Because the aim of this study is to estimate causal effects, we have to make the four standard causal identifiability assumptions (conditional exchangeability, positivity, counterfactual consistency, and no interference). These are described in detail elsewhere (32). As mentioned earlier, the conditional exchangeability assumption may be violated here, which means there may be some residual confounding left after adjustment. Additionally, the no interference assumption, which states that the vaccination status of one individual does not have an effect on the outcome of another individual, is also probably violated, as is usually the case in vaccine effectiveness studies (71). This, however, has nothing to do with the observational nature of this study. The same violation would occur if the randomized target trial was actually carried out, with no commonly accepted solution to this problem having been proposed in the literature (71, 72). The results of this study will therefore have to be interpreted cautiously.

#### 2.6.6 Negative control outcome analysis

To quantify the amount of residual confounding, a negative control outcome analysis will be performed (73). In this strategy, the analysis is repeated with suitable negative control outcomes, which are variables that ideally have the same causes as the actual outcome of interest, but are not directly caused by the exposure of interest. We will use *medically attended urinary tract infection* as a negative control outcome for all considered analyses. In particular, we will use inpatient and outpatient diagnoses (ICD-10 code N39.0) with an associated prescription for a relevant antibiotic to identify the infections (see online supplement). This outcome has been used in other vaccine effectiveness studies for influenza- (73, 74), herpes zoster- (75), and pneumococcal vaccines (76). These studies additionally used other negative control outcomes, such as hip fractures and fractures of the hand or wrist. We choose not to use these outcomes here, due to their potentially large association with corticosteroid medication (77), which we can only partially adjust for in our analysis through the category of received medications. Our strategy to identify the exact dates of outpatient diagnosis is again described in the online supplement.

## 3 Discussion

The proposed study has multiple strengths. One of the biggest strengths is its large sample size. With approximately 50,000 MS patients, 300,000 CIRD patients, 80,000 IBD patients and potentially millions of control patients, this study is, to the best of our knowledge, the largest of its kind. Because it is based on data from a German health insurance provider, it also contains information on the medications prescribed to each patient, as well as their acquired infections and comorbidities. This large sample size makes a detailed disease specific population based comparison of the vaccine effectiveness with appropriate controls possible. The available information also makes adjustment for many of the relevant confounders feasible. The very limited amount of inclusion criteria additionally facilitates the generalizability of the obtained results.

A limitation of this study is the potential of unmeasured or unknown confounding. As discussed earlier, we are not able to adjust for all confounders that were identified by our assumptions about the causal data generation process. For example, it is impossible to measure social contact behavior from the available data. It is also possible, if not likely, that the DAG we specified is partially wrong or fails to include other, currently unknown, confounders. This is a frequent problem in observational studies, although it is not always acknowledged (32). We will attempt to quantify the impact of this potential source of bias through pre-planned sensitivity analyses.

A further limitation is the potential of misclassification of the vaccination status due to individuals getting vaccinated through their company physicians, or in rarer cases in hospitals or pharmacies. Because some individuals will be misclassified as “unvaccinated,” it is possible that the estimates of the vaccine effectiveness will be biased downwards. However, we expect this to be a minor issue, because most individuals in Germany get vaccinated through their primary care physician. Under the assumption that the misclassification rate does not differ between the considered disease groups, we would also not expect bias of the contrast between the vaccine effectiveness estimates.

Additionally, it is important to note that the BARMER data is not a probability based sample of the general German population. It is possible that there are substantial differences between the general German population and people enrolled in the BARMER, which theoretically makes the generalization of the results of this study to the general German population difficult. Nevertheless, due to its large size and nation-wide adoption, we believe that this is a minor problem.

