Treatment Assignment	Individual randomization, stratified on disease status (MS, IBD, CIRD or none of these).	To emulate randomization we adjust for multiple confounders using a combination of matching and g-computation.
Start and end of trial	(1) Herpes zoster vaccine effectiveness trial: 01.12.2018–31.12.2021^a^ (2) Influenza vaccine effectiveness trials:*^b^* (a) 01.09.2015–31.05.2016 (b) 01.09.2016–31.05.2017 (c) 01.09.2017–31.05.2018 (d) 01.09.2018–31.05.2019	
Start and end of follow-up	Start of follow-up: time of assignment to treatment strategy. End of follow-up: The earliest of death, loss-to-follow-up or administrative end-of-follow-up (end of the respective study).	
Outcomes	(1) Herpes zoster vaccine effectiveness: medically attended Herpes zoster infection (2) Influenza vaccine effectiveness: (a) medically attended influenza infection (b) severe medically attended influenza infection	
Causal contrast	(1) The ratio between the vaccine effectiveness (1 - the relative risk to develop the outcome at time *t* given the treatment) in the diseased group (individual has either MS, IBD or CIRD) and the non-diseased group (2) The vaccine effectiveness for each of the three disease groups (MS, IBD, CIRD), stratified by the categorized severity of received medication in regards to immunosuppressive effect. Both contrasts will be estimated as *intention-to-treat* and *per-protocol* effects. The target estimand is the average causal effect on the treated (ATT).	
Statistical analysis	Computing formal contrasts of simple Kaplan-Meier estimates.	Time-dependent 1:1 matching by days without replacement. Controls will be matched exactly by age in years, biological sex, place of residence, and disease status. The matched sample will be analyzed using a Cox model with additional adjustment for further confounders. G-computation based on this Cox model and a non-parametric estimate of the baseline hazard will be used to estimate the target estimand. Both *intention-to-treat* and *per-protocol* effects will be estimated by different censoring schemes as described in Section 2.6.3.
Sensitivity analysis	None.	The entire analysis will be repeated using *medically attended urinary tract infection* as a negative control outcome to assess the robustness of the confounder adjustment employed.

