#### 2.5.2 Treatments

The “treatments” in this study are the two different types of vaccines of interest. We will not differentiate between different subtypes of vaccines in the influenza vaccine effectiveness trials. Any vaccine against influenza will be considered an “influenza vaccine”, regardless of its' underlying mechanism and irrespective of which company created the vaccine. In the herpes zoster trial we will only consider the inactivated recombinant zoster vaccine (Shringrix^®^) (41). In Germany, vaccinations are usually provided by physicians in primary care. Physicians receive a reimbursement for each vaccination from the statutory health insurance of the individual being vaccinated. To this end, a standardized reimbursement code [German: Gebührenordnungsposition (GOP)] is used and transferred to the insurance as part of a reimbursement claim. We will use these codes to identify vaccinations in our study population, using both codes applying uniformly for all regions in Germany and codes only used for specific regions and time periods. The reimbursement codes used are listed in the online supplement.

There is, however, one special case that needs to be mentioned. Whenever individuals get vaccinated through a company physician (in German: Betriebsärzte), the reimbursement code is not transferred to the insurance company of the individual. The reimbursement is instead taken care of by the companies themselves. Additionally, a few pharmacies and hospitals also vaccinate individuals without sending reimbursement codes to the insurance company (42). Because these vaccinations never show up in the individuals data of the health insurance, the vaccination status of these individuals will be misclassified in the analysis. We expect this issue to have a minor impact, because the majority of vaccinations are performed by primary care physicians in Germany. There is currently no official data available to quantify the proportion of vaccinations performed in these different settings. Due to the complex nature of the proposed analysis strategy, as described in Section 2.6, it is also not possible to apply standard methods of quantitative bias analysis to quantify the effects of this potential bias (43). To still get a rough estimate of the potential impact of this misclassification, we will repeat the main analysis after removing 10% of all vaccination dates from the available data in a sensitivity analysis.

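### Equal under-recording of vaccination does not in general leave the vaccine-effectiveness ratio unbiased, and one 10% deletion covers only part of the problem

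*Protocol article*

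**What the plan says.** Table 1 (section 2.2) defines the first causal contrast as "The ratio between the vaccine effectiveness (1 - the relative risk to develop the outcome at time" *t*) in the diseased group over that in the non-diseased group.

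Section 2.5.2 explains why some vaccinations are invisible: "Whenever individuals get vaccinated through a company physician (in German: Betriebsärzte), the reimbursement code is not transferred to the insurance company of the individual", and a few pharmacies and hospitals also vaccinate without sending a claim. It adds that "There is currently no official data available to quantify the proportion of vaccinations performed in these different settings". Because of the complexity of the analysis, it says, "it is also not possible to apply standard methods of quantitative bias analysis to quantify the effects of this potential bias". In its place, "we will repeat the main analysis after removing 10% of all vaccination dates from the available data", to get a rough idea of the impact. It does not say how the 10% is chosen, or whether the share varies by age or disease group.

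The Discussion accepts that "it is possible that the estimates of the vaccine effectiveness will be biased downwards", and then says of the comparison that, if the rate of misclassification is the same in each disease group, "we would also not expect bias of the contrast between the vaccine effectiveness estimates".

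**The concern.** Under-recording places truly vaccinated people among the apparent controls. How far this dilutes VE depends on the share of vaccinated people among those controls, and that share depends on coverage as well as on the recording rate. Controls are matched within disease group (section 2.6.1), so each group's VE is diluted according to its own coverage. The dilution factor also depends on the VE itself. An equal recording failure can therefore dilute the two VEs by different proportions, and their ratio moves.

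The protocol gives no reason to assume equal coverage, and unequal VE is the hypothesis under study. At stake is a shift in the primary contrast that a reader, relying on the Discussion, would not think to allow for. The one planned check uses a single, unstratified value.

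**Working it through.** The protocol states no bias figure, so there is none to reproduce.

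**Inputs.** All numerical inputs are assumptions:
- Under-recording *u*: 5% to 30%.
- True coverage *p*: 20% to 50% for influenza, 5% to 10% for zoster. Section 2.6.1 says only that a fairly small proportion is vaccinated.
- True VE: 0.3 to 0.5 for influenza, 0.7 to 0.85 for zoster.

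**Formulas.** Recorded vaccinations are taken as true.
- Vaccinated share among apparent controls: c = u·p / (u·p + 1 − p).
- With R₀ the risk if unvaccinated, risk in apparent controls is R₀(1 − c·VE). So observed RR = (1 − VE)/(1 − c·VE), and observed VE = VE(1 − c)/(1 − c·VE).
- Deleting 10% of recorded dates replaces u by 1 − 0.9(1 − u).

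Two consequences follow. Equal u with unequal p gives unequal c. Even with equal c, the factor (1 − c)/(1 − c·VE) differs when VE differs: at c = 0.05 and VE 0.3 vs 0.5, the ratio is 0.594 instead of 0.600.

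**One case in full.** VE 0.4 in both groups (true ratio 1.000), coverage 0.5 (diseased) vs 0.2 (not), u = 0.10 in both:
- c = 0.05/0.55 = 0.091 and 0.02/0.82 = 0.024.
- Observed VE = 0.4 × 0.909/0.964 = 0.377 and 0.4 × 0.976/0.990 = 0.394. Ratio 0.958, a bias of −4.2%.
- After deletion, u = 1 − 0.9 × 0.9 = 0.19, c = 0.160 and 0.045, VE = 0.359 and 0.389. Ratio 0.923, a further shift of −3.6%.

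**Equal under-recording in both groups** (diseased / non-diseased):

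| Coverage | True VE | True ratio | Observed ratio at u = 5%, 10%, 20%, 30% | Bias from u = 5% to 30% |
|---|---|---|---|---|
| 0.3 / 0.3 | 0.4 / 0.4 | 1.000 | 1.000 throughout | 0 |
| 0.3 / 0.3 | 0.3 / 0.5 | 0.600 | 0.597, 0.595, 0.590, 0.586 | −0.4% to −2.4% |
| 0.5 / 0.2 | 0.4 / 0.4 | 1.000 | 0.978, 0.958, 0.920, 0.886 | −2.2% to −11.4% |
| 0.5 / 0.2 | 0.3 / 0.5 | 0.600 | 0.583, 0.568, 0.539, 0.514 | −2.8% to −14.3% |
| 0.10 / 0.05 (zoster-like) | 0.70 / 0.85 | 0.824 | 0.822, 0.821, 0.819, 0.817 | −0.1% to −0.8% |

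**What the 10% deletion shows:**

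| Coverage (VE 0.4 in both) | u, diseased / non-diseased | True bias of ratio | Shift on deletion |
|---|---|---|---|
| 0.5 / 0.2 | 10% / 10% | −4.2% | −3.6% |
| 0.5 / 0.2 | 20% / 20% | −8.0% | −3.0% |
| 0.5 / 0.2 | 30% / 30% | −11.4% | −2.5% |
| 0.3 / 0.3 | 5% / 20% | +3.8% | −0.4% |
| 0.5 / 0.2 | 5% / 20% | 0 | −4.1% |

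In the first three rows the shift has the right sign, but it shrinks as the true bias grows. In the fourth it is small and of the wrong sign. In the fifth it suggests a bias that is not there.

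**The case against.** Four points can be made for the plan.

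- **The deletion check works in the case that the Discussion describes.** A reader might infer that it cannot reveal the bias, or would reassure whatever the truth. The figures do not support that: with equal under-recording near 10% the shift (−3.6%) is close to the bias (−4.2%), and section 2.5.2 promises only a rough estimate. This stands. The weakness is confined to rates well above 10% and to rates that differ by group. Nor does the text say that the deleted dates are picked at random.
- **For zoster there is little to find.** A reader might fault the check because it hardly moves VE at low uptake, but the bias itself is then below about 1%. Contamination c can never exceed coverage p, so large values of c cannot arise there. This stands, and the point is chiefly about influenza.
- **The larger sizes need large assumed differences.** With coverage 30% vs 20%, VE 40% in both groups and u of 5% to 10%, the ratio is 0.995 to 0.990, a bias of 1% or less. The protocol expects most vaccinations to take place in primary care. This stands as a limit on the size, not as a defence of the sentence.
- **The closed form does not capture the design.** It takes one constant c, unrelated to risk, and ignores daily matching, pair censoring and covariate adjustment. Re-running the analysis on altered data does respect the design. So the formula does not overturn the remark in section 2.5.2 about standard bias methods; it shows that an approximate calculation is available alongside the rerun.

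**Conclusion.** The sentence in the Discussion is wrong as a general statement about the primary contrast. An equal misclassification rate is not enough: in general, true coverage and true VE must also be equal across groups. If the rate is read as the contaminated share of controls, equal true VE is still required.

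Under the assumed inputs and equal under-recording of 5% to 30%, the relative bias of the ratio is below about 1% for zoster, 0.4% to 2.4% for influenza when only VE differs, and 2% to 14% when influenza coverage is 50% vs 20%. The sign reverses if the non-diseased group has the higher coverage and VE is equal. These are static approximations, and none of the inputs comes from the protocol.

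The single 10% deletion is useful but too narrow. Company vaccination reaches employed people, so under-recording may well vary with working age, and hence between disease groups whose age and employment mix differ. That is the situation in which one uniform deletion can mislead.

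**What to change.** 1. Replace the no-bias sentence with its conditions: equal under-recording, equal coverage and equal true VE across groups, and say that otherwise the ratio may be biased.
2. In the deletion analysis, report the VE contrast as well as each VE.
3. Repeat the deletion over a range, for example 5%, 10%, 20% and 30%, including unequal shares by disease group and deletion concentrated in working ages. State how the dates are selected.
4. Add the correction VE = VE_obs/(1 − c + c·VE_obs) by disease group over the same range, labelled as an approximation that ignores daily matching and censoring.
5. Optionally, report the contrast in people past working age, noting that pharmacy and hospital vaccinations remain unrecorded there. Section 2.6.2 already plans age-specific VE, so this extends it to the contrast between disease groups.

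The cost is some extra reruns, a spreadsheet-level calculation, and fewer events in the age-restricted analysis. The primary estimator does not change.
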